#### 7.1.3. Other study parameters

On admission a detailed anamnesis should be taken relating to blood transmittable viral infections, other relevant diseases (relevant surgical interventions in the past five years, history of blood transmittable viral infections, anaphylactic reactions to the use of plasma products) and the use of other medication.

- To correct for known prognostic factors (age, preceding diarrhea, positive serology of different micro-organisms, antibodies against gangliosides) we will ask questions about antecedent events, as diarrhea and upper respiratory tract infection and perform laboratory measurements (serology against *Campylobacter jejuni*, cytomegalovirus (CMV), Epstein-Barr virus (EBV), *Mycoplasma pneumonia* and IgG, IgM and IgA antibodies against GM1, GD1a and GQ1b.) IENF density in skin biopsies (additional).

## 7.2. Randomization, blinding and treatment allocation

All GBS patients in need of IVIg treatment are potentially eligible for this study. All participants will be evaluated after first IVIg treatment and scored following the modified EGOS model. Patients with a poor prognosis according to this model will be randomized to receive a second IVIg dosage or placebo. For that a randomization website is used (see the signed agreement with CTCM). A computer-generated list of random assignments (block randomization per site) is prepared in advance. When a PI registers a patient to the website a box number is generated and an email with this box number will be sent automatically to the local pharmacist (and the central pharmacy of the Erasmus MC, the coordinating investigator, the co-investigator, Sanquin and the registering PI). The box number corresponds to the randomization list and the local pharmacist will prepare the study medication according to the randomization allocation. The PI will prescribe the trial medication in the same dosage as the first treatment (2 g/kg administered in 5 consecutive days). The coordinating investigator, the co-investigator, the PI and the trial coordinator of Sanquin as well as the patient will be blinded to the treatment.

Blinding will be broken in case of a Serious Adverse Event considering the severity of the adverse event and the likeliness of a relation to IVIg treatment after conference between the investigators, Sanquin and the treating neurologist. The treating neurologist will then be unblinded and is responsible for treatment of the possible side effects of the IVIg treatment.

Blinding will not be broken in case of a TRF, a TRF is defined as (1) improvement in the GBS disability score of at least one grade or improvement in the MRC sum score (0-60) of more than 5 points after completion of the first IVIg course, followed by a worsening in the GBS disability score of at least one grade or a decrease in the MRC sumscore of more than 5 points within the first months after onset of disease or (2) stabilization of the clinical course for more than 1 week after completion of the first IVIg course, followed by a worsening of at least one grade of the GBS disability score or more than 5 points on the MRC sumscore. When a TRF occurs during the trial medication course, the trial medication will be stopped and an open IVIg course will be started, as this is standard treatment for a TRF. This decision should always be taken after consultation with the trial coordination.

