#### **B. Relative contra-indications for second IVIg dose:**

- Patients known to have severe kidney dysfunction (GFR below 40 ml/min).
- Pre-existing risk factors of thrombo-embolic complications or severe ischemic heart disease.

These patient groups run a greater risk (although they are still rare) to develop serious complications like acute tubular necrosis and thrombo-embolic events. To prevent this they should be pre-treated with fluids and infusion rate of the trial medication must be adjusted.

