### **6.4. Summary of known and potential risks and benefits**

Nanogam and GPO are produced by Sanquin Plasma products, Amsterdam. Nanogam and GPO are manufactured from plasma of voluntary, non-remunerated donors. The viral safety of the products have been established by donor selection and screening for HIV1-2, HTLV I/II and hepatitis B and C, by plasma pool screening for HIV, HCV, HBV and Parvo B19 at RNA /DNA level, and by effective inactivation and/or removal of viruses with several physico-chemical methods in the manufacturing process.

The most common adverse effects occur soon after infusion with Nanogam and can include chills, headache, fever, vomiting, allergic reactions, nausea, arthralgia, low blood pressure and moderate low back pain. Side effects are rare during or after infusion of albumin products. Mild reactions such as flush, urticaria, fever, and nausea are usually temporarily and often associated with infusion rate.

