#### **6.7. Preparation and labelling of Investigational Medicinal Product**

Every participating hospital owns a buffering stock of IVIg (Nanogam®) and GPO (shelf lives of 3 and 4 years). When a patient is eligible for entering the second RCT phase of this study, the patient will be randomized to get a second IVIg course or placebo. The local pharmacist will prepare the trial medication according to the randomization allocation.

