#### **7.7. Premature termination of the study**

Severe complications attributable to IVIg are rare. Yet, clinical evidence of an association between thrombo-embolic complications (myocardial infarction, stroke, lung embolism, deep venous thrombosis) and IVIg treatment exists. This association is probably attributable to the relative increase in blood viscosity because of the high influx of immunoglobulins. It is imaginable that a second dosage of IVIg in a short period further increases the chance of developing such a severe complication, especially in patients with pre-existing risk factors of thrombo-embolic complications (older age, hypertension, diabetes mellitus, history of vascular disease or thrombo-embolic illnesses, patients with acquired or inborn pre-thrombotic disease, patients with long term immobilization, deep hypovolemic state and patients who have illnesses which cause increased viscosity of the blood). Extra precautions will be taken in patients with pre-existing risk factors for thrombo-embolic complications and patients with kidney function disturbances. When

significantly more severe complications occur most likely attributable to the second IVIg dosage the study will be prematurely terminated.

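### Section 7.2 gives the treating neurologist no immediate route to the allocation: an SAE can open the blind only after a conference that includes the manufacturer

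*Protocol*

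**What the plan says.** **Opening the blind.** Section 7.2 states: "Blinding will be broken in case of a Serious Adverse Event considering the severity of the adverse event". The second consideration is the "likeliness of a relation to IVIg treatment after conference between the investigators, Sanquin and the treating neurologist". The section goes on: "The treating neurologist will then be unblinded and is responsible for treatment of the possible side effects of the IVIg treatment". Sanquin makes both trial products; section 6.4 says "Nanogam and GPO are produced by Sanquin Plasma products, Amsterdam". Section 7.2 lists the coordinating investigator, the co-investigator, the PI, Sanquin's trial coordinator and the patient as blinded.

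**Who holds the allocation.** Section 6.7 says: "The local pharmacist will prepare the trial medication according to the randomization allocation". Section 7.2 repeats this and describes how the box number reaches the pharmacist. Neither section says that a clinician may obtain the allocation from the pharmacist.

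**TRF.** Section 7.2 keeps the blind closed for a TRF. If the TRF occurs during the trial course, "the trial medication will be stopped and an open IVIg course will be started, as this is standard treatment for a TRF", always after consultation with the trial coordination. Treatment of a TRF after the trial course is not stated.

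**Hazard and precautions.** Section 7.7 considers it imaginable that "a second dosage of IVIg in a short period further increases the chance of developing such a severe complication" and lists myocardial infarction, stroke, lung embolism and deep venous thrombosis. Section 4.3B requires fluid pre-treatment for patients at higher risk and adds that the "infusion rate of the trial medication must be adjusted".

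**The concern.** Section 7.2 makes the treating neurologist responsible for treating side effects of IVIg, yet the neurologist learns the allocation only after a three-party discussion that includes the product's manufacturer. The events that section 7.7 fears can need decisions within minutes or hours, and whether the patient has just received a second IVIg course may bear on them. The conference must also judge a likely relation to IVIg while the trial roles named in section 7.2 are blinded, so they do not know whether the trial infusion was IVIg at all.

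The TRF rule raises a related, separate point. Open IVIg is started on top of a trial course of unknown content, while section 7.7 treats cumulative IVIg as a possible hazard and goes no further than a second dosage.

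**Working it through.** The protocol states no sample size, power or event figure on this point, so there is none to reproduce. The check compares the sections and then works through the dose arithmetic.

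**1. Is there any faster route to the allocation?**

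| Place in the protocol | What it adds |
|---|---|
| 7.2 | SAE, then severity and relation weighed, then conference, then neurologist unblinded |
| 6.7 | Pharmacist prepares from the allocation; no release to the clinician described |
| 6.6 and 6.8 | Marked not applicable |
| 8.1 to 8.6 | Reporting, follow-up and DSMB; no code-break procedure |

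The only described route is the one through the conference. Three situations are left without the allocation: the time before the conference is held, an SAE for which the conference decides against release, and a TRF.

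**2. Exposure when open IVIg starts for a TRF during the trial course**

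Inputs:
- First course: 2 g/kg (section 4.2B).
- Trial course: 8 ml/kg per day for five days (sections 3 and 6.5) of a 50 mg/ml product (section 5.1).
- Open course: section 7.2 gives no dose. I assume 2 g/kg; section 6.5 says that the trial course's regimen is also used for TRF.

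Trial dose per day = 8 ml/kg × 50 mg/ml = 400 mg/kg = 0.4 g/kg. Over five days, 5 × 0.4 = 2.0 g/kg, which agrees with the stated 2 g/kg.

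With k trial infusions given before the TRF:
- placebo arm, prior IVIg = 2.0 g/kg, total = 2.0 + 2.0 = 4.0 g/kg;
- IVIg arm, prior IVIg = 2.0 + 0.4k g/kg, total = 4.0 + 0.4k g/kg.

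| k | Prior, placebo (g/kg) | Prior, IVIg (g/kg) | Total, placebo (g/kg) | Total, IVIg (g/kg) |
|---|---|---|---|---|
| 0 | 2.0 | 2.0 | 4.0 | 4.0 |
| 1 | 2.0 | 2.4 | 4.0 | 4.4 |
| 2 | 2.0 | 2.8 | 4.0 | 4.8 |
| 3 | 2.0 | 3.2 | 4.0 | 5.2 |
| 4 | 2.0 | 3.6 | 4.0 | 5.6 |
| 5 | 2.0 | 4.0 | 4.0 | 6.0 |

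Two full courses come to 2.0 + 2.0 = 4.0 g/kg, the highest exposure that section 7.7 discusses. In the IVIg arm the total exceeds this as soon as one trial infusion has been given.

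**3. How many patients?**

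This cannot be derived. Section 1 gives a TRF rate of about 10%, for all GBS patients after a single course. Applied to the 87 to be randomised it gives 0.10 × 87 = 8.7 TRFs in all. The open-IVIg rule covers only those that fall within the five-day trial course, and the protocol does not give that share.

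**The case against.** The defence has several sound points.

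- **Treatment does not wait for the conference.** A reader might infer that the neurologist must treat a complication blind, or that treatment is delayed. The text supports neither as a general statement. Once release is agreed the neurologist is unblinded and treats with that knowledge. Section 7.2 makes unblinding follow the conference, not treatment, and gives no duration for it. What stands is that no immediate route to the allocation is described.
- **The manufacturer does not decide alone.** The investigators and the treating neurologist take part in the conference.
- **Keeping the blind closed for a TRF is defensible.** A reader might call sections 7.2 and 7.7 contradictory. They are not: a stated possible hazard and a rescue rule subject to consultation can coexist. There is a tension, because section 7.7 stops at a second dosage.
- **Precautions are not confined to trial medication.** Section 7.7 promises extra precautions for patients at risk in general terms, and the fluid pre-treatment in section 4.3B is tied to the patient. Only the infusion-rate clause names the trial medication, so it would go too far to say that the open course has no cover at all.
- **The 10% is not a contamination rate.** A reader might infer that about four patients per arm get open IVIg, or that a tenth of the placebo arm gets the exposure meant to be withheld. Both count every TRF, whereas the rule applies only during the trial course. Nor does every such IVIg-arm patient reach three full courses, since the trial medication is stopped.
- **A safety table by number of courses received is not missing here.** It would be analysis-plan content, and the grouping would be post-randomisation and confounded by the TRF itself. Section 9 fixes intention-to-treat.

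**Conclusion.** The point holds in a limited form, as an inexpensive safety improvement rather than a flaw in the comparison. Section 7.2 ties release of the allocation to a prior conference that includes the manufacturer, and I find no other route in the protocol. This is a stated rule rather than a detail left to another document.

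The TRF part is smaller. During the trial course, open IVIg is started with prior exposure unknown to the neurologist: 2.0 g/kg in one arm and 2.0 to 4.0 g/kg in the other. The totals of 4.0 against 4.0 to 6.0 g/kg rest on the assumed 2 g/kg open course. The sections need to be reconciled; they do not contradict each other outright. No patient count can be attached to either part.

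**What to change.** 1. Amend section 7.2 so that the treating neurologist can obtain the allocation without delay from the local pharmacist when an SAE requires it. The conference, the notification of the investigators and Sanquin, and the documentation of the reason would follow. Section 6.7 should name the pharmacist's part in this. The cost is protocol wording and an instruction to pharmacies; the downside is possibly a few more unblinded patients.
2. Reconcile the TRF rule in section 7.2 with sections 4.3B and 7.7, so that the protocol says whether the hazard discussion and the infusion-rate precaution extend to an open course given after part of the trial course. What the clinical rule should be is for the sponsor and the clinicians; none is proposed here. The cost is wording only.

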## 7.3. Study procedures

When patients are included in the study they will undergo the following extra procedures;

- Throat swabs
- Blood collection

Blood collection will take place before start of standard IVIg treatment (visit 1), after standard IVIg treatment (visit 2), after two weeks (visit 3), after 4 weeks (visit 4) and after 3 months (visit 6). Mostly it will be possible to collect blood for the study simultaneously with vena punctures performed in the scope of the medical work-up.

- CSF collection

At admission virtually all patients undergo a lumbar puncture as part of the standard medical workup; extra CSF will be collected for the SID-GBS study. In this way there is no need for an extra spinal puncture. For the study a small

- sample (5 cc) of CSF is sufficient. If no lumbar puncture was performed for various reasons, no lumbar puncture will be performed in the scope of this study.
- EMG examination generally is comparable with the situation outside a study, but may be more extensive in some patients. This depends on the local procedures in the participating hospitals. An EMG guideline is developed in a way that a minimum set of nerves is tested to enable classification of electrophysiological data according to Hadden[28].
  - Additional for patients of 18 years and older and included in a hospital in Rotterdam.

Two times two skin biopsies for determination of IENF density. Punch biopsy of 3 mm 10 cm above the lateral malleolus and paraspinal after local anesthesia with 1% lidocaine. Skin biopsy for determination of IENF density is a minimal invasive procedure. Estimated time 10 minutes. There is a very small risk of getting an infection. Some people get a scar at the site of the biopsy (often less than 3mm, conform the size of the punch biopsy).

#### **7.4. Withdrawal of individual subjects**

Subjects can be withdrawn from the study at any time for any reason if they wish to do so without any consequences. The PI can decide to withdraw a subject from the study for urgent medical reasons. In all cases, the reasons why patients are withdrawn must be recorded on the CRF and in the patients' medical record.

#### **7.5. Replacement of individual subjects after withdrawal**

Not applicable

#### **7.6. Follow-up of subjects withdrawn from treatment**

For all subjects who are prematurely withdrawn from treatment, the reason will be documented carefully. The patients who had at least one dose of study medication will at least be included in the safety evaluation.

#### **7.7. Premature termination of the study**

Severe complications attributable to IVIg are rare. Yet, clinical evidence of an association between thrombo-embolic complications (myocardial infarction, stroke, lung embolism, deep venous thrombosis) and IVIg treatment exists. This association is probably attributable to the relative increase in blood viscosity because of the high influx of immunoglobulins. It is imaginable that a second dosage of IVIg in a short period further increases the chance of developing such a severe complication, especially in patients with pre-existing risk factors of thrombo-embolic complications (older age, hypertension, diabetes mellitus, history of vascular disease or thrombo-embolic illnesses, patients with acquired or inborn pre-thrombotic disease, patients with long term immobilization, deep hypovolemic state and patients who have illnesses which cause increased viscosity of the blood). Extra precautions will be taken in patients with pre-existing risk factors for thrombo-embolic complications and patients with kidney function disturbances. When

significantly more severe complications occur most likely attributable to the second IVIg dosage the study will be prematurely terminated.

## **8. SAFETY REPORTING**

### **8.1. Section 10 WMO event**

In accordance to section 10, subsection 1, of the WMO, the investigator will inform the subjects and the reviewing accredited METC if anything occurs, on the basis of which it appears that the disadvantages of participation may be significantly greater than was foreseen in the research proposal. The study will be suspended pending further review by the accredited METC except insofar as suspension would jeopardize the subjects' health. The investigator will take care that all subjects are kept informed.

### **8.2. Adverse and serious adverse events (SAE)**

Adverse events are defined as any undesirable experience occurring to a subject during a clinical trial, whether or not considered related to the investigational drug. All adverse events reported spontaneously by the subject or observed by the investigator or his staff will be recorded.

A serious adverse event is any untoward medical occurrence or effect that at any dose;

- results in death
- is life threatening (at the time of the event)
- requires hospitalization or prolongation of existing inpatients' hospitalization\*
- results in persistent or significant disability or incapacity
- is a congenital anomaly or birth defect
- is a new event of the trial likely to affect the safety of the subjects, such as an unexpected outcome of an adverse reaction, lack of efficacy of an IMP used for the treatment of a life threatening disease, major safety finding from a newly completed animal study, etc

*\*all patients in this trial are hospitalized, this is not considered to be a serious adverse event.*

All SAE's will be reported to the accredited METC that approved the protocol, according to the requirement of that METC.

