### 3. STUDY DESIGN

A double-blind randomized placebo-controlled trial design will be used in selected patients with a poor prognosis. In patients with a good prognosis the study will have an observational design.

- All GBS patients in need of IVIg treatment, according to the treating neurologist, in a standard dosage of 2 g/kg in 2-5 consecutive days are potentially eligible for this study after obtaining informed consent.
- When patients sign 'Informed consent' they principally agree to be randomized to get a second IVIg dose or placebo when having a poor prognosis at day 7 and to be followed up for 6 months.
- Patients with the poorest prognosis based upon the modified EGOS (mEGOS 6-12) after the first IVIg course will be randomized to get a second course of IVIg (Nanogam®) in a dosage of 8 ml/kg (=0,4 g/kg) for 5 days or placebo (GPO®) in a dosage of 8 ml/kg for 5 days in a blinded fashion.
- mEGOS must preferentially be assessed 7 days after start of first IVIg course, with a range to 8 or 9 days. Trial medication needs then to be started within 24 hours when indicated according to the mEGOS score (see figure 4).
- Patient follow-up will be 6 months.
- Total patient inclusion will end when 44 patients with a poor prognosis received a second IVIg dosage.
- After covariate adjustment, to deal with variation between patients in baseline risk and to increase statistical power, data of the placebo group and the intervention group will be compared.

This is shown in the flowchart (table 2).

[figure not shown]

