### **Data collection**

1. Questionnaires encompassing patient demographics, preceding events, indicators of disease severity, disease progression and outcome will be filled out at predefined standard time points by the PI and after monitoring will be send to the coordinating center at Erasmus MC.
2. Blood samples, CSF and a throat swap will be send to the coordinating center. The specimen will be analyzed at the Erasmus MC at the department of neuro-immunology and microbiology. In addition DNA will be stored for future gene polymorphism studies. We expect that the collected samples will be of interest for future research in the next decade, so we will store the material for 15 years, when informed consent is obtained.
3. An EMG is performed in the standard work-up of GBS patients. The PI will be asked to perform an EMG following predefined guidelines to enable classification of electrophysiological data according to Hadden[28] as indicative of primary demyelinating disease, equivocal, primary axonal, unexcitable and normal. Guidelines were developed in collaboration with the clinical neurophysiology department of the Erasmus MC.
4. After discharge from the hospital, patients will be asked to visit the outpatient clinic of the local hospital for follow-up. When a patient is fully recovered according to the GBS disability score, the MRC sum score and the ONLS score at 3 months, they will be discharged from further follow-up, presuming GBS is a monophasic disease.
5. Patients of 18 years or older included in hospitals in Rotterdam, will be asked to have a skin biopsy (3 mm punch) to determine intraepidermal nerve fibre (IENF) density. Yet, unpublished research from our group showed prognostic value of IENF density in skin biopsies. We aim to expand this study. Skin biopsy for determination of IENF density is a standard - minimal invasive - procedure requiring local anesthetics and resulting in a small scar. Estimated time 10 minutes. The skin biopsy protocol includes a skin biopsy at the distal leg and a lumbar paraspinal biopsy. The biopsies will be taken in the first week of admission and after 6 months. Skin biopsies are additional to the standard protocol, patients can decide to participate in the SID-GBS study without giving approval for taking skin biopsies. Therefore patient information and informed consent forms are strictly separate.

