#### 7.1.2. Secondary study parameters/endpoints

- Percentage of patients that improve:  
at least 1, 2, 3 or 4 points on the GBS disability score at 4, 8, 12 and 26 weeks,  
at least 4, 8 or 12 points on MRC sum score (ranging from 0-60) at 4, 8, 12 and 26 weeks,  
at least 2, 4 or 6 points on ONLS score (ranging from 0-12) at 4, 8, 12 and 26 weeks.
- Percentage of patients needing artificial ventilation.
- Time (number of days) on respirator.
- Time (number of days) on intensive care unit.
- Percentage of patients that die because of GBS.
- Time (number of days) to hospital discharge.
- Percentage of patients with secondary deterioration due to treatment-related fluctuations (TRF).
- Development of complications possibly related to a second IVIg course.
- Serum IgG levels at 5 different time points.

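### The footnote to the hospitalisation criterion in section 8.2 has no limit, so an event that is serious only through a longer stay or a readmission could be classed as non-serious

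*Protocol*

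**What the plan says.** Section 8.2 lists six grounds on which an untoward event is serious. The third is that the event "requires hospitalization or prolongation of existing inpatients' hospitalization". An asterisk at the end of that line leads to the footnote: "all patients in this trial are hospitalized, this is not considered to be a serious adverse event".

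Three other places bear on how the footnote works:

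- Section 3 fixes the observation period: "Patient follow-up will be 6 months". Under Data collection it describes what happens once patients go home: "After discharge from the hospital, patients will be asked to visit the outpatient clinic of the local hospital for follow-up".
- Section 7.1.2 makes leaving hospital an endpoint: "Time (number of days) to hospital discharge".
- Section 7.7 names the harms that a second IVIg course might make more likely: "thrombo-embolic complications (myocardial infarction, stroke, lung embolism, deep venous thrombosis". Section 4.3B adds acute tubular necrosis in at-risk patients.

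**The concern.** The footnote presumably exists so that sites do not report the GBS admission itself as an SAE. As worded it reaches further. The asterisk stands on a line that joins admission and prolongation, and the word used for what is exempted has no stated referent. The justification, that everyone is in hospital, describes patients at entry and during the trial infusions but not over the whole 6 months.

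For a patient who is already admitted, prolongation is often the ground that makes a moderately severe complication serious. After discharge, readmission plays that part. If a site takes the footnote to switch off the whole line, such an event goes into the AE record as non-serious and the reporting steps that depend on SAE status do not follow. The complications named in sections 7.7 and 4.3B include some that could fall in this gap.

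**Working it through.** No figure needs recomputing. The check is to read the criterion, the footnote and the follow-up schedule together and to trace what depends on the classification.

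**Step 1: scope of the asterisk.** Admission and prolongation form a single criterion with a single asterisk. Nothing in the footnote separates them, and nothing elsewhere in section 8 does.

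**Step 2: scope in time.** The footnote has no end point. Sections 3 and 7.1.2 show that patients are discharged within the trial and seen as outpatients. The premise therefore lapses at each patient's discharge, while the exemption as written does not.

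**Step 3: two readings.** On the narrow reading, only the existing GBS admission is exempt. On the broad reading, the whole line is exempt.

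| Event | Narrow reading | Broad reading |
|---|---|---|
| Admission for GBS itself | Not an SAE | Not an SAE |
| Non-life-threatening deep venous thrombosis that prolongs the stay | SAE | AE, non-serious |
| Reversible renal event that prolongs the stay | SAE | AE, non-serious |
| Readmission after discharge for an event that meets no other criterion | SAE | AE, non-serious |
| Fatal or life-threatening lung embolism, disabling stroke | SAE | SAE, under another criterion |

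The readings part only for events with no other ground for seriousness. The remaining five grounds in section 8.2 (death, threat to life, lasting disability, congenital anomaly, and a new event bearing on subjects' safety) are untouched.

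**Step 4: what depends on SAE status.**

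- Section 8.2: SAEs are reported to the METC.
- Section 8.4: the annual safety report lists and tabulates suspected serious adverse reactions.
- Section 7.2: an SAE is the trigger for conferring about breaking the blind.

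**Step 5: what does not depend on it.**

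- Section 8.2: every AE is recorded. Section 8.5: every AE is followed up.
- Section 7.1.2: complications possibly related to the second course are an endpoint in their own right.
- Section 8.6: the DSMB reviews the safety data every 6 months.
- Section 7.7: the termination rule speaks of severe complications, not of SAEs.

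**The case against.** The strongest reply is that the narrow reading is the natural one. The footnote first states a fact, that everyone is hospitalised, and then says that this fact is not an SAE. It does not say that prolongation or readmission is exempt. A protocol would hardly list a criterion and void it in the same section. This stands: a reader might infer that the footnote cancels the hospitalisation criterion for every patient throughout the trial, but the text does not establish that. It only fails to rule it out.

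The narrow reading does not settle the matter, however. Section 3 shows that patients are already admitted when they are asked to take part, and section 8.2 defines an AE as arising during the trial. The GBS admission would hardly be an AE anyway, so on the narrow reading the footnote does little work. A site asking what it exempts may well look to the whole line. Section 4.1 reports 67 hospitals willing to participate, so the same event could be classified differently from one site to another.

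The second reply is that safety information survives by other routes (step 5). This also stands, and it confines the consequence to classification and to the three uses in step 4. It bears on two further inferences that a reader might draw:

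- *That the comparison of SAEs between the arms would be biased.* Section 7.1.2 specifies no such comparison. Its safety endpoint is complications, which does not rest on the footnote.
- *That SUSARs would be lost.* A SUSAR must be unexpected against the Investigator's Brochure, which is not available here. Sections 7.7 and 10.4 already describe thrombo-embolic and renal events as recognised risks of IVIg.

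**Conclusion.** The point holds as a wording defect in the rule that governs SAE reporting. The footnote is unbounded: it covers prolongation as well as admission, and its premise stops being true at discharge. Applied literally, an adverse event that is serious only through a longer stay or a readmission could be kept as a non-serious AE. It would then miss METC reporting, the annual list where it is a suspected reaction, and the trigger for considering unblinding.

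The footnote applies to every patient in the trial, including the roughly 87 to be randomised. How many events would be misclassified cannot be derived: the protocol gives no complication rates and calls severe complications rare. The conclusion assumes only that some sites would take the footnote literally. Sample size, primary endpoint and primary analysis are unaffected.

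It is still worth correcting, because the events at risk of misclassification include kinds that the protocol itself names as possible harms of the tested treatment.

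**What to change.** Reword the footnote in section 8.2 so that it exempts only the initial admission for GBS. State there that prolongation of that stay by an adverse event, and any readmission during the 6-month follow-up, meet the hospitalisation criterion. Put the same instruction on the case report form.

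The cost is a sentence in section 8.2, a matching CRF instruction and a modest rise in the number of SAE reports. If the narrow meaning was always intended, the change only makes it explicit. It alters no treatment, endpoint or analysis.
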